# Combined Topical Growth Factor and Protease Inhibitor in Chronic Wound Healing: Protocol for a Randomized Controlled Proof-of-Concept Study

**DOI:** 10.2196/resprot.8327

**Published:** 2018-04-27

**Keywords:** leg ulcers, growth factors, protease inhibitors

## Abstract

**Background:**

Leg ulcers due to venous disease are chronic wounds that can take 6 or more months to heal. Growth factors have been used to try and improve this healing; however, many such studies have failed, and that is thought to be due to enzymes in the wound that degrade the growth factors and prevent them from working.

**Objective:**

This is a proof-of-concept study that will evaluate the treatment of chronic leg ulcers with topically applied growth factors that are combined with a therapy to prevent their inactivation in the wound. This combined therapy has the potential to speed up the healing of these wounds and thereby improve the quality of life of patients and reduce the costs to the health system.

**Methods:**

This will be a double-blind, placebo-controlled, randomized controlled proof-of-concept study comparing growth factor with protease inhibitor wound dressings to growth factors with standard wound dressings.

**Results:**

The project was funded by the Canadian Institutes for Health Research and enrollment is expected to be initiated in 2018. It is expected that results will be available in 2021.

**Conclusions:**

It is expected that the results of this trial will inform as to whether modifying the wound environment through the use of protease inhibitors increases the effectiveness of topically applied growth factors in the healing of chronic wounds.

**Trial Registration:**

ClinicalTrials.gov NCT02845466; https://clinicaltrials.gov/ct2/show/NCT02845466 (Archived by WebCite at http://www.webcitation.org/6yOPhSBUA)

## Introduction

### Chronic Wounds

Chronic wounds are prevalent across the Canadian health care continuum [1] and have a significant financial and social burden on the health care systems, patients, and their families [1-4]. Chronic wounds are defined as wounds that are poorly healing and persisting for 3 months or more [1]. Clinical subtypes of chronic wounds include the following: (1) venous leg ulcers (VLUs), (2) arterial ulcers, (3) diabetic foot ulcers (DFUs), and (4) pressure ulcers. VLUs and DFUs are the most prevalent chronic wounds and have high rates of recurrence ranging from 16% at 1 year to 60% at 5 years for VLU [5,6] and greater than 50% after 3 years for DFU [2]. The cost attributed to chronic wound management in Canada is considerable [7] with more than Can $1 million per year estimated for each Canadian hospital to treat just pressure ulcers and surgical wound infections [8]. The total annual cost associated with DFU-related care was $547 million CAD, or $21,371 CAD annual cost per prevalent case in 2011 [3]. It is imperative that new cost-effective treatments that significantly increase healing rates and reduce amputation and hospital admission rates are required. Cost-effective wound management is a key priority for Canadian health care organizations [9-11].

### Venous Leg Ulcers

Lower limb ulcers occur in 1% to 2% of adults, with 70% of leg ulcers being of venous etiology [12]. The point prevalence in the population over 70 years of age is approximately 1% [13]. The majority of VLUs are long-standing; 60% of ulcer patients in the community experience ulcers that remain unhealed for more than 26 weeks, and 23% for more than 2 years [14]. In their Canadian Bandaging Trial, Harrison and colleagues identified that most patients were over 65 years in age and over two-thirds had experienced leg ulcers for many months. Half of the affected population had a leg ulcer history spanning from 5 to 10 years and one-third exceeding 10 years [15]. Some ulcers require skin grafting to achieve healing. The delayed healing of leg ulcers and the high costs associated with outpatient, inpatient, and community care represent a significant economic burden to the health care system, estimated to be in the order of 1% of total health care budget in Western societies [16]. Current clinical treatment guidelines for venous ulcers involve the use of compression bandaging to counter the effects of venous hypertension and dressings to promote an optimum wound-healing environment. Despite treatment with compression, healing times are still long, with only 45% of ulcers healing in 13 weeks [17]. There is a need for cost-effective therapies that improve these ulcer-healing rates.

### Diabetic Foot Ulcers

Diabetes is one of the most burdensome chronic diseases in Canada with an estimated 7% of the population living with diabetes [17]. Over their lifetime, 15% to 25% of people with diabetes will develop a DFU [18], and 12% of those patients will require lower extremity amputation due to the progression of their chronic DFU [19]. The current standard for treating DFUs is pressure off-loading in addition to treatments for wound infection, maintaining adequate blood supply, local wound care, and control of the diabetes. There is a need for cost-effective therapies that improve ulcer-healing rates and prevent amputations.

### Impaired Healing in Chronic Wounds

Wound healing is a complex process that has 4 phases [20]. The initial hemostatic phase occurs immediately after the injury, and during this phase, growth factors released from platelets that bind to the wound site initiate the wound-healing process. Growth factors are soluble signaling proteins that instruct cells during cell development and influence the process of wound healing [21]. The second phase is the inflammatory phase during which white cells migrate to the wound and release additional growth factors as well as remove foreign material. The third phase is the proliferative phase, which involves formation of granulation tissue, wound matrix formation, and epithelialization. The final phase is remodeling, which is an ongoing phase during which excessive material is removed and collagen synthesis and breakdown occur as the wound is remodeled. The last 3 phases overlap over time.

Chronic wounds are typically characterized by an ongoing and excessive inflammatory phase while proliferative phase is trying to occur at the same time [22]. This profound inflammatory phase is thought to play a key role in delaying healing. During this phase, there is evidence of elevated levels of inflammatory cytokines [23-25], elevated levels of proteases including matrix metalloproteases (MMPs) and elastase [22,26-28], impaired function of cellular components including fibroblasts and epithelial cells [29-31], and reduced levels of growth factors [22,32,33]. Contaminating bacteria also affect the inflammatory phase [34-36]. In chronic wounds, impaired healing is considered to be caused by a number of factors that are a result of this prolonged inflammatory phase: (1) degradation of extracellular matrix (ECM) proteins that form the new healed tissue, (2) degradation of healing regulators including peptide growth factors and endogenous protease inhibitors [22,27,28,37], and (3) impaired responses of the cellular components within the wounds [30,31,38].

### Increased Protease Activity in Wounds and Wound Fluid

The levels of a number of proteases and their inhibitors have been measured in different chronic wound types. These have assessed levels of proteases within chronic wound fluid (CWF), have compared levels between acute and chronic wounds, and have compared levels between nonhealing and healing chronic wounds. Results indicate that CWF has consistently elevated levels of MMPs (MMP-1,-2,-8,-9,-13) and neutrophil elastase compared with acute wound fluid [22,26,28]. Studies have demonstrated a reduction in MMPs during healing phases of VLUs and DFUs and reduced levels of tissue inhibitors of metalloproteinases (TIMPs) in nonhealing or reduced MMP/TIMP ratios during healing [23,37]. Although the levels vary between individuals, these studies indicate an association between lower levels of MMPs and healing of VLUs and DFUs.

In addition, the elevated levels of proteases within CWF are inhibitory to the healing process within chronic wounds by degrading ECM proteins and regulators of the healing process. Therefore, reduction of protease levels in CWF has the potential to improve the healing process in these wounds.

### Reduction in Protease Activity

A number of potential agents have been identified to reduce or modulate MMP activities and to control the proteolytic environment in the chronic wound. These include the antibiotic doxycycline [39], the wound dressing Promogran (Systagenix) [40], and nanocrystalline silver [41]. Promogran is a protease-modulating matrix wound dressing composed of 55% collagen and 44% oxidized regenerated cellulose in an absorbent open-pored, sterile, freeze-dried matrix. Once the matrix comes in contact with the wound exudate, it absorbs the fluid and forms a soft gel. The gel physically binds to and inactivates the damaging proteases (MMPs) and elastase and also binds to growth factors, protecting them and preventing them from being degraded [42]. The growth factors are then released back into the wound in an active form [40]. One small clinical study has shown a decrease in protease activity in CWF samples taken from patients with chronic venous ulcers treated with Promogran [43]. This study demonstrated a significant reduction of elastase and MMP-9 activity after 5 days of treatment with Promogran. Accelerated healing in both VLUs and DFUs has been observed in clinical trials with Promogran alone [44-46].

A small observational study of 15 patients indicated that Promogran, in combination with Regranex, had a stimulating effect on DFUs, with rapid wound area reduction [47]. Moreover, a small randomized prospective clinical study showed that the combination of Promogran and autologous growth factors from platelets was significantly better than the Promogran or autologous growth factors from platelets alone in DFUs [48]. Larger analyses do not show a significant benefit from applying topical autologous growth factors from platelets to wounds [49]. It is possible that the protease inhibition enabled the effect that was observed in this study.

### Enhancing Delayed Healing

Wound repair is controlled by a number of growth factors that include platelet-derived growth factor (PDGF), keratinocyte growth factor, transforming growth factor β, and a number of other growth factors. The increasing understanding of the role of growth factors, including PDGF and transforming growth factor-β, in wound repair has resulted in their clinical application for the treatment of chronic wounds. Over the past decade, there have been an increasing number of randomized controlled trials using PDGF in the format of becaplermin gel (Regranex). Becaplermin (recombinant human PDGF-BB, rhPDGF-BB) is a homodimer produced by recombinant DNA (deoxyribonucleic acid) technology utilizing the insertion of the gene for the B chain of PDGF into the yeast *Saccharomyces cerevisiae*. The biological activity of rhPDGF-BB is similar to the naturally occurring PDGF and includes formation of granulation tissue at the wound site and stimulation of the wound-healing processes [50].

There have been a number of trials for the treatment of nonhealing DFUs demonstrating statistically significant effects in phase 2, phase 3, and phase 4 clinical trials [51,52]. These trials have demonstrated the efficacy of rhPDGF-BB gel at 30 g/g and 100 g/g when used in conjunction with optimal wound care. Patients treated with rhPDGF-BB gel had a significant increase in complete healing compared with patients given placebo gel (50% vs 36% at dose of 100 g/g) and a decrease in the time to complete healing by 30% (14 weeks vs 20 weeks) [53]. It was concluded that rhPDGF-BB gel used in conjunction with optimal wound care is effective and well tolerated in patients with full-thickness DFUs. A systematic review and meta-analysis has concluded that rhPDGF-BB gel improves the healing of DFUs [54].

In other types of chronic wounds such as pressure ulcers, studies using rhPDGF-BB gel showed promising results [55,56]. In patients with chronic venous ulcers, 2 small randomized, placebo-controlled trials have evaluated the application of rhPDGF-BB gel (100 mg/g). In both studies, a greater percentage of patients treated with rhPDGF-BB gel achieved complete healing compared with patients in the placebo-treated group, but this was not statistically significant [57].

There is an ongoing safety review and warning from the US Food and Drug Administration regarding the amount of rhPDGF-BB gel that can be used. In a retrospective study of patients treated with rhPDGF-BB gel, the incidence rate for all cancers was 10.2 per 1000 compared with 9.2 per 1000 in matched controls [58]. An increased rate of mortality secondary to malignancy was observed in patients treated with 3 or more tubes of rhPDGF-gel in a postmarketing retrospective cohort study. A warning is now included in the product label, indicating the increased rate of mortality secondary to malignancy in patients who use 3 or more tubes of rhPDGF-BB gel [58].

Double-blind, placebo-controlled trials of other growth factors in venous ulcers—epidermal growth factor (EGF) [59], human growth factor [60], granulocyte-macrophage colony-stimulating factor (GMCSF) [61], and transforming growth factor-beta2) [62]—have not demonstrated significant improvements in ulcer healing.

### Lack of Response of Wounds to Topical Growth Factors

This lack of response may be due to a number of factors including the following: degraded ECM; inefficient presentation of growth factors to the cell surface receptors in ways that do not reflect normal in vivo cell surface receptor activation; use of single growth factors instead of more physiologic combinations of growth factors; delivery of free growth factors instead of growth factors bound to or associated with appropriate ECM proteins; and the rapid loss of growth factors from the wound site, possibly due to diffusion or degradation. There is some evidence of mild to complete degradation in venous ulcer wound fluid of proteins such as vitronectin [63] and EGF [64]; therefore, the lack of response to individual topical growth factors for VLUs may be due to the breakdown of the growth factors by proteases in the chronic wound environment [65]. The lack of response of VLU to topical growth factors may be reversed by reducing the protease activity in CWF, and it is postulated that the response of DFU to topical growth factors will be enhanced by reducing protease activity.

### Point-of-Care Testing for Protease Level

A novel point-of-care testing tool, WOUNDCHEK Protease Status (WOUNDCHEK Laboratories), has been developed to determine whether wounds have an increased total protease activity. This test indicates that the total protease activity is either elevated or not elevated based on a predetermined level. It does not give a quantitative measure of total or individual protease levels. If the predetermined levels are meaningful, the test may help to guide the usage of topical agents including growth factors and protease inhibitors. There are 2 registered, ongoing, and unpublished noncomparative studies of the WOUNDCHEK Protease Status test that started recruiting in March 2012, with estimated completions in March 2013 [66], although the results are not as yet available. The studies are designed to enter 250 patients—one study for VLU and another for DFU. Each study aims to determine whether wounds with elevated total protease levels treated with protease modulating therapies have improved clinical healing trajectories at 4 weeks, which are indicative of healing outcomes at 12 weeks. There is a need for randomized controlled trials to determine whether the use of protease inhibitors guided by WOUNDCHEK Protease Status test is accurate and sensitive as compared with using a laboratory protease level assay. If WOUNDCHEK Protease Status test demonstrates clinical utility, it could be used in routine real-time wound management practice.

Recent work in the principal investigator’s laboratory has identified a potential biomarker that with a single test can determine the state of healing of a wound. In this study, GMCSF levels in CWF were elevated in nonhealing compared with healing wounds with apparent separation between the 2 groups. Overall, 90% of nonhealing wounds had a level above an observed threshold. This biomarker test, in combination with a point-of-care protease test such as WOUNDCHEK Protease Status, would provide tools for the clinician to make informed decisions on the use of topical protease inhibitors and growth factors in real time. This would represent a major advance in current wound management and be a completely novel paradigm of therapy for VLU and DFU.

### Novel Approach to Improving Healing

The novel concept of this study is to translate the different elements of research on topical growth factors, protease inhibitors, and point-of-care testing in VLU and DFU into a paradigm of treatment that combines topical growth factors and protease inhibition. This may enable topical growth factors to be effective where they have not been previously in VLU and may enhance the benefit that has been shown in DFU. This model is based on modifying CWF to have more of the characteristics of acute wound fluid. A proof-of-concept study is needed to evaluate whether the use of topical protease inhibitors in both VLUs and DFUs inhibits protease activity and protects topically applied growth factors from degradation and whether this can be monitored by existing or future potential point-of-care tests.

### Hypothesis

A protease inhibitor in combination with PDGF will reduce protease levels and prevent growth factor degradation in chronic VLUs and DFUs as compared with a placebo.

### Primary Aim

The primary aim of this study was to determine whether the topical application of a protease inhibitor in combination with a topical growth factor prevents the degradation of applied growth factors in chronic VLUs and DFUs.

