### Planned Interventions

Participants will be randomized to receive a protease inhibitor or a placebo for 4 weeks of the study, in combination with a topical growth factor. All participants will receive just the topical growth factor for 2 weeks to obtain baseline data on growth factor and protease levels in the wound fluid.

The interventions patients will receive are as follows:

All participants will have Regranex gel (Smith & Nephew) containing a recombinant human PDGF for topical administration, applied to their leg or foot ulcers on a weekly basis for 6 weeks. Regranex is a nonsterile, sodium carboxymethylcellulose-based topical gel. Each gram of Regranex gel contains 100 g of rhPDGF-BB. This is applied by measuring a length of gel from a 15 g tube and is applied at a rate of 0.25 cm length of gel per cm^2^ of ulcer area. A maximum of 2 tubes will be used for each patient, and each patient will have his or her own treatment tubes to ensure that the limit of 2 tubes is not exceeded.Participants randomized to receive the protease inhibitor will receive Promogran (Johnson & Johnson) cut to the size of the ulcer and applied over the rhPDGF-BB.Participants in the placebo arm will receive Aquacel (ConvaTec) dressing applied in a similar manner to the Promogran. This dressing is very similar in appearance to Promogran and has no active protease inhibition function.VLU participants will have an absorbent pad and a 4-layer compression bandage system (Profore, Smith & Nephew) applied over the dressings.Diabetic foot ulcer participants will have an absorbent pad fixed with tape applied over the dressings.

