### Randomization Method

Randomization will occur after the first week in which the participant’s compliance with optimal standard therapy is assessed. If the participant is not compliant at this point, he or she will not be randomized into the study. The research coordinator will randomly assign eligible participants using a computer-generated randomization tool. Following eligibility screening by the research coordinator, the system will generate a unique number. The research coordinator then telephones the treatment nursing staff and reports the number. In turn, treatment research nurses refer to a manual of unique numbers generated by an independent biostatistician before study activation to determine the study intervention allocated to the randomized patient. The randomization schedule will be stratified by wound type (VLU or DFU) in variable blocks of 4 and 6. Randomized patients will receive all treatments during the study period according to the intervention they were allocated. The patients, study investigators, research coordinator, laboratory technologists, and assessing research nurses will be blinded to the treatment allocation. Only the treating team members are not blinded.

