### Inclusion and Exclusion Criteria

Inclusion criteria were as follows:

Men and women aged ≥18 yearsUlcer size 1-64 cm^2^Ulcer extends through both the epidermis and dermis, with no exposed tendon or boneUlcer duration >3 months and <12 monthsUlcer located between and including the knee and ankleFor VLUs—venous refilling time <25 s on photoplethysmography or abnormal venous insufficiency duplex scanFor DFUs—confirmed type 1 or type 2 diabetes mellitus with a hemoglobin A1C <12%Wounds that have not been treated with Promogran in the previous 4 weeksPatients able to give informed consent

Exclusion criteria were as follows:

Ankle-brachial index <0.8Ulcer with local or systemic signs of infectionPatients who have been previously treated with rhPDGF-BB gelPatients receiving corticosteroids or immune suppressantsHistory of autoimmune diseaseUncontrolled diabetes (baseline hemoglobin A1C >12%)Severe rheumatoid arthritisUncontrolled congestive heart failureMalnutrition (albumin <2.5 g/dL)Unable to adhere to the protocolKnown sensitivities to the wound dressings used in the trialHistory of any previous malignancyPregnant or lactating woman

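### The knee-to-ankle inclusion criterion is not limited to venous ulcers, so as written it shuts out the diabetic foot ulcers that the aims, stratification and analysis require

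*Protocol article*

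**What the plan says.** All references are to the Protocol article.

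- **Question.** Under Primary Aim, the study is to establish whether the combined treatment "prevents the degradation of applied growth factors in chronic VLUs and DFUs". Under Hypothesis, the combination is expected to "prevent growth factor degradation in chronic VLUs and DFUs as compared with a placebo". Three of the Secondary Aims also name both wound types.
- **Treatment.** Under Planned Interventions, the gel is "applied to their leg or foot ulcers on a weekly basis for 6 weeks", and there is a separate dressing rule: "Diabetic foot ulcer participants will have an absorbent pad fixed with tape applied over the dressings". Under Treatment Period, DFU participants have off-loading optimised in the first week.
- **Randomisation.** The schedule is "stratified by wound type (VLU or DFU) in variable blocks of 4 and 6" (Randomization Method).
- **Outcomes and analysis.** Outcome Measures gives DFUs their own four-week threshold (area reduction above 50%, against 40% for VLUs). Data Analysis puts wound type in the repeated-measures models. Planned Subgroup Analyses provides for VLU and DFU subgroups if the responses differ.
- **Eligibility.** Inclusion and Exclusion Criteria contains one location item: the ulcer must lie in the region bounded by knee and ankle, with both included. It has no wound-type prefix. The next two items do: one for VLUs (venous testing) and one for DFUs, which asks only for "confirmed type 1 or type 2 diabetes mellitus with a hemoglobin A1C <12" percent.

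**The concern.** The eligibility list and the rest of the protocol describe different populations. A foot ulcer below the ankle is the typical case that the DFU provisions are written for, and it fails a criterion that applies to every participant. If screening follows the list, the trial loses one of its two target populations without any decision to drop it. If screening follows the aims, the trial enrols patients who do not meet its own criteria. In the first case no conclusion about foot ulcers would be possible. In the second, the reported population would not match the registered rules.

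**Working it through.** **Step 1: whom the location item binds.** The items on age, size, depth, duration and location are unprefixed. The venous-test and diabetes items that follow are marked by wound type. The authors therefore marked type-specific criteria where they meant them, and the unmarked location item reads as applying to all.

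**Step 2: is there an exemption elsewhere?** The DFU item concerns diabetes type and HbA1c and does not mention site. The exclusion list, Planned Interventions, Treatment Period, Compliance and Outcome Measures do not address ulcer location as an eligibility matter. None lifts the rule for DFUs.

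**Step 3: apply the location item to each site.**

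- Venous ulcer between knee and ankle: passes.
- Ulcer at the ankle in a person with diabetes: passes, because the ankle is included.
- Ulcer above the ankle in a person with diabetes: passes on location. The list does not say how wound type is assigned.
- Ulcer on the foot below the ankle: fails.

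**Step 4: what this does to the plan.** With no foot ulcers, the DFU stratum holds at most ulcers at or above the ankle in people with diabetes. If it is empty, the stratification factor and the wound-type term each have a single level, the DFU healing threshold applies to nobody, and the condition for the subgroup analysis cannot be assessed.

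**Step 5: does the sample size change?** Inputs from Sample Size: difference 25%, SD 35%, power 80%, significance level 5% (taken as two-sided; the article does not say).

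- n per group = 2 × (1.960 + 0.842)² × (35/25)² = 2 × 7.85 × 1.96 ≈ 30.8, so 31. This reproduces the stated figure. A one-sided test would give 25, which does not match.
- Loss allowance: 1 − 31/40 = 22.5%, in line with the stated allowance of just over 20%.

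Wound type does not enter this calculation. Eligibility screening comes before the randomisation number is generated, and the target is 40 per group overall. Patients who fail the location item are never counted among the 80, so 31 and 40 stand.

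**The case against.** The strongest reply is that the intent is plain. A separate dressing, a stratum, off-loading and a healing threshold for DFUs show that foot ulcers were meant to be enrolled, and the location item most likely lost a VLU prefix. That is probably right. It lowers the chance that foot ulcers are really turned away, but it does not remove the contradiction: screening follows written criteria, and nothing written limits this one. Nor is it a detail left to a fuller document, since the article states the rule.

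A reader might infer more than the document supports:

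- **Loss of power.** Assuming half of the participants were to be DFUs and were lost, 15.5 per arm would remain after loss, with t-test power of about 49% against 79% at 31 per arm. The article gives no VLU:DFU split, and ineligible patients are replaced rather than lost. If VLUs fill all 80 places, power is as planned. Recruitment could be slower, but without the split this cannot be sized.
- **Damage to every outcome.** The planned t test of percentage area change and the chi-squared tests of protease status and GMCSF status do not use wound type. A mislabelled stratum does not in itself bias a randomised comparison.
- **Leg ulcers placed in the DFU stratum.** The DFU item can be read as a condition on an ulcer already classed as a DFU, not as a definition of one. Nothing says that a venous ulcer in a person with diabetes is stratified as a DFU. It is fair only to say that the assignment rule is not stated.
- **Every DFU enrolled being a violation.** Ulcers at the ankle qualify, so this holds only below it.
- **The abstract as further proof.** Its objective, to "evaluate the treatment of chronic leg ulcers with topically applied growth factors", may simply use an umbrella term in a condensed text and adds little.

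**Conclusion.** The contradiction holds and sits in one line of Inclusion and Exclusion Criteria; the Primary Aim itself is not at fault. Taken literally, the line excludes all ulcers on the foot below the ankle, leaves the DFU stratum empty or confined to ulcers at or above the ankle, and removes the basis for any answer about foot ulcers. Taken by intent, each DFU below the ankle is an eligibility breach. The size of the problem is the loss of the DFU part of the question, not a loss of power: 31 evaluable and 40 recruited per group are unaffected. The conclusion rests on reading an unprefixed item as general, which the prefixes on the next two items support. It does not depend on any assumed mix of wound types. It should be corrected before the first participant is screened.

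**What to change.** Reconcile Inclusion and Exclusion Criteria with the aims before enrolment:

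1. Limit the knee-to-ankle criterion to VLUs by giving it the same kind of prefix as the items that follow it.
2. Add a DFU location criterion that admits foot ulcers. The investigators should set the exact boundary at the ankle; the document supports no particular line, and the current text admits ankle ulcers.
3. State under Randomization Method that wound type for stratification follows these definitions, so that each ulcer has one assigned type.

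The cost is a short eligibility amendment and a matching change to the screening form, with no added patients, procedures or analyses. The article expects enrolment to begin in 2018, so the change can be made before screening starts.
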